## Materials and methods

### Overview and ethics

LION is a sham-controlled, participant-masked, randomized controlled trial (NCT03968874), investigating primarily, the efficacy of morning bright light therapy (MBLT) to improve sleep quality, cognitive function, and quality of life in Veterans with mTBI, and secondarily, the feasibility and acceptability of implementing a fully remote clinical trial within the VA. Participants were randomized and allocated 2:1 to active (MBLT) or sham (negative ion generator) study arms, with a target total sample size of n = 120 participants with complete pre- and post-intervention data (~80% of the data has been collected so far). Primary outcomes were changes between groups from baseline to post-intervention (28 days), and baseline to follow-up (56 days). All participants that expressed interest, screened eligible, and were enrolled in the study were processed according to the Standard Protocol Items and Recommendations for Interventional Trials (SPIRIT) guidelines (Fig 1). This project is sponsored by the Military Traumatic Brain Injury Initiative (MTBI^2^) and approved by a joint Institutional Review Board (IRB) at the VA Portland Health Care System (VAPORHCS; #4268 and #4002) and Oregon Health & Science University (OHSU; #19411), as well as the Department of Defense Office of Human Research Oversight (OHRO). All participants provided, or will provide, verbal and written informed consent prior to participation.

**Fig 1 pone.0305305.g001:**
[figure not shown]
SPIRT outcomes across time. The Standard Protocol Items: Recommendations for Interventional Trials (SPIRIT) timeline for LION.

The total target sample size of n = 120 participants is based on a priori power analyses considering mean insomnia severity index score as the primary outcome (see below). Using a two-sided students t-test design comparing MBLT to sham (pre- to post-intervention), the minimal detectable clinically relevant between-group difference was set at 7% with a standard deviation of 12% within MBLT and 7.3% within sham groups. This approach achieves β = 0.15 with α = 0.05 (i.e., 85% power; 15% probability of incorrectly accepting the null hypothesis) [49,50].

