To our knowledge, the field of sleep medicine is without a fully powered, sham-controlled, masked, randomized controlled trial establishing feasibility, acceptability and efficacy of MBLT to improve sleep quality in Veterans with mTBI. Furthermore, to our knowledge, a fully remote randomized controlled trial device intervention protocol has not yet been successfully implemented in Veterans with mTBI–a challenging population not only due to significant participant disability/burden, but also due to the logistical and regulatory challenges of device management and electronic data capture behind the Veterans Affairs (VA) firewall. We sought to fill both gaps by implementing LION (Light vs Ion therapy), whose protocol is described herein. This trial proposed to acquire complete data in n = 120 Veterans allocated 2:1, active-intervention (MBLT, n = 80) versus sham-intervention (deactivated ion therapy, n = 40). MBLT delivered white light (10,000 lux at the eye), whereas the negative ion generator was fully deactivated, but modified to appear “on”, i.e., via installation of a small fan to generate a quiet, whirring sound, as well as a small LED status light. This sham-intervention was modeled from prior work by Lam et al., [28] in which bright light or sham-intervention therapy was compared to fluoxetine for the treatment of depression. Participants in both groups engaged with devices to the same extent (i.e., over 60 minutes within 2 hours after waking) throughout the 28-day intervention period, with the same degree of expectancy and study team interaction. The brand of the light box was chosen due to being commercially available, in use for decades (including within the VA), and previously validated for illuminance metrics and spectral power density [25]. Dose, timing, and duration were all established from prior work investigating the effect of MBLT for the treatment of insomnia, circadian entrainment, and seasonal affective disorder [46–48].

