### Outcomes

#### Primary

LION’s primary outcome was designated as an improvement in sleep following MBLT compared to sham. This was accomplished via several means, though self-reported sleep disturbances via the Insomnia Severity Index (ISI) remained primary [53]. The ISI is a 7-item measure, each item a 5-point Likert scale (0–4) with a total score range of 0–28 where higher scores indicate worse sleep [54,55].

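### The stated 85% power does not follow from the stated difference, standard deviations and sample size, which give about 95% to 97.5%

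*Protocol article*

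**What the plan says.** All the inputs are in the article. The sample-size paragraph, under Overview and ethics after the Fig 1 legend, says "The total target sample size of n = 120 participants is based on a priori power analyses", with the mean Insomnia Severity Index (ISI) score as the outcome. The test is given as "Using a two-sided students t-test design comparing MBLT to sham (pre- to post-intervention", and "the minimal detectable clinically relevant between-group difference was set at 7% with a standard deviation of 12% within MBLT and 7.3% within sham groups". The result is "This approach achieves β = 0.15 with α = 0.05 (i.e., 85% power".

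The Introduction gives the split: "allocated 2:1, active-intervention (MBLT, n = 80) versus sham-intervention (deactivated ion therapy, n = 40". Overview and ethics makes clear that 120 counts completers: "target total sample size of n = 120 participants with complete pre- and post-intervention data".

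Two other places bear on the calculation. Randomization, allocation, and masking expects more variability under MBLT and argues that 2:1 allocation therefore gives a small gain in power. Outcomes, Primary describes the ISI as having a "total score range of 0–28 where higher scores indicate worse sleep".

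**The concern.** A power statement should be reproducible from the inputs printed beside it, and this one is not. Either a printed input was not the one used, or the printed power is wrong. The article calls the trial fully powered, and this paragraph is the only support for that.

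The choice of input also matters elsewhere. The allocation section's power argument depends on the arms having different SDs. If the calculation in fact used one SD for both arms, the two sections contradict each other. A reader who wants the power of any subset, such as participants with mTBI, gets very different answers depending on which SD is real.

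**Working it through.** **Inputs.** Difference d = 7; SDs 12 (MBLT) and 7.3 (sham); two-sided alpha 0.05 (all from the sample-size paragraph). n = 80 and 40 completers (Introduction; Overview and ethics). Percentages are treated as plain units. If they are percentages of the scale range, converting to ISI points leaves power unchanged.

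**1. Looking for the plan's own 85%.** It appears with SD 12 in both arms:
- SE = 12 × √(1/80 + 1/40) = 2.324
- noncentrality = 7 / 2.324 = 3.012, df = 118
- power from the noncentral t = 84.8%

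The normal-approximation sample size agrees. Sham n = (1 + 1/2) × (1.960 + 1.036)² × 12² / 7² = 39.6, rounded up to 40, hence 80 + 40 = 120. A common SD of 12% thus reproduces both 120 and 85%, but it makes no use of the 7.3%.

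**2. Using both stated SDs, Welch t-test.**
- SE = √(12²/80 + 7.3²/40) = √(1.800 + 1.332) = 1.770
- noncentrality = 7 / 1.770 = 3.955, Satterthwaite df = 113
- power = 97.5%

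**3. Using both stated SDs, other forms at a total of 120.**

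| Calculation | Power |
|---|---|
| Pooled Student t, simulated with SDs 12 and 7.3 | about 95% |
| Common SD = root mean square of the two, 9.93 | 95.1% |
| Common SD = df-weighted pooled, 10.68 | 91.9% |
| SDs swapped between arms (Welch) | 91.4% |
| One-sided Welch | 98.9% |
| 60/60 allocation, Welch | 96.9% |

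The nearest to 85% is 91.4%, more than 6 points away.

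**4. Total needed for 85% at 2:1 with SDs 12 and 7.3.**
- Welch: 72 (48/24, power 85.5%).
- Pooled Student, simulated: 84.8% at 87 (58/29) and 86.2% at 90 (60/30), so about 87 to 90. At 48/24 this test has only about 76% to 77%.

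**5. Dropout.** 120 is already the completer target, so attrition cannot fill the gap. For scale, raising 72 to 120 would need 40% loss (72 / 0.60 = 120), while the article reports 83% retention (116 of 140).

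**6. The allocation argument.**

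| Basis | 80/40 | 60/60 | Does 2:1 help? |
|---|---|---|---|
| SDs 12 and 7.3, Welch | 97.5% | 96.9% | slightly |
| SDs 12 and 7.3, pooled Student (simulated) | about 95% | about 97% | no |
| SD 12 in both arms | 84.8% | 88.7% | no |

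The claim of a small gain from 2:1 holds only in the first row, where power is not 85%. The 85% holds only in the last row, where 2:1 costs about 4 points.

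**The case against.** **The error is harmless.** On both stated SDs the power exceeds 85% in every form tried, and with SD 12% in both arms it is essentially as claimed. Either way 120 completers give about 85% or more for a 7% difference. This stands. It makes the point a reporting correction and not a threat to the trial.

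**The article names a Student t-test.** A reader might infer from the Welch result that only 72 participants were needed, that the target is 48 too high, or that the true detectable difference is about 5.3%. Those figures belong to the Welch form alone. Under the pooled Student test, 85% needs about 87 to 90 participants and the detectable difference is about 6%. The allocation argument points towards Welch, but the article does not settle which form was meant.

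**An apparent surplus for mTBI.** Enrolment was widened to people without TBI, and 71 of the 104 interim completers have mTBI (47 and 24). It is tempting to conclude that excess power makes an mTBI-only analysis affordable. The documents do not support that. Projecting the interim shares to the full target gives roughly 54/27 (80 × 47/69 = 54.5; 40 × 24/35 = 27.4). Power there is about 89% (Welch), 82% (Student) or 69% (SD 12% in both arms). The answer turns on the very input in doubt.

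**The percentage may be defined elsewhere.** The article is condensed and cites sources not available here. The meaning of 7% may be given in the full protocol, so the unit is a query and not an error. If it means 7% of the 0 to 28 range, it is 1.96 points. If it means change from baseline, it is a different quantity.

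**Conclusion.** The point holds as an inconsistency in the article's own figures. The printed inputs give about 97.5% (Welch) or about 95% (pooled Student), not 85%. The 85% at 120 requires SD 12% in both arms, which conflicts with the stated sham SD of 7.3% and with the argument that 2:1 allocation raises power. That a common SD of 12% was in fact used is an inference from its reproducing both numbers; the article does not say so.

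The results assume normally distributed changes, 80/40 completers and two-sided alpha 0.05. On the stated inputs the discrepancy is conservative. It gives no ground for calling the trial under-powered, for changing enrolment, or for claiming a reserve for an mTBI-only analysis.

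**What to change.** State which SDs and which form of t-test the calculation used, then make one of two corrections:

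- If SDs of 12% and 7.3% were intended, correct the power at 80/40 to about 97.5% (Welch) or about 95% (pooled Student). Keep the allocation section's power argument only if the Welch form was used.
- If SD 12% in both arms was used, correct the sham SD to 12%, keep 85%, and remove or revise the claim that 2:1 allocation increases power.

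In both cases keep the a priori 7% difference. Replacing it with a value worked back from n = 120 would discard the clinical rationale. Say what the percentage refers to on the ISI, preferably with its equivalent in points.

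If power for the mTBI participants is reported, give it for the SDs and test actually confirmed, with the assumed numbers per arm.

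The cost is a few sentences of text. Enrolment and analysis do not change.

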### Recruitment and sample selection

Participants were recruited nationwide, with additional local efforts from flyers and clinician referrals within the VAPORHCS, OHSU, and surrounding Portland-Metro area (Fig 2). The most successful recruitment methods included repositories, referrals, internet-based advertisements, flyers, and radio ads, all described in more detail below. Recruitment began 6/1/2019 and remains ongoing.

**Fig 2 pone.0305305.g002:**
[figure not shown]
Participant flow chart. Diagram illustrating steps involved with LION, including when participant study visits are held, which outcomes are collected when, the duration of each study period as well as when equipment and biospecimens are shipped to/from participants place of residence.

#### Repositories

Several large participant repositories developed from prior and ongoing studies within the VAPORHCS were utilized, which collectively house contact information from over 1500 Veteran participants to date who consented to being recontacted for future research such as this study. Regulatory approvals were in place to share identifiable data and participant contact information with approved LION study team personnel. Additional tools that have or may be used in the future for participant recruitment include ResearchMatch.org and the VA Informatics and Computing Infrastructure (VINCI) system. Both services enable research coordinators to connect with potentially eligible participants either via personal profile information (research match) or through opt-out letters (VINCI).

#### Referrals

Several opportunities for participant referrals are approved and utilized. First, clinicians within the VAPORHCS and associated community-based outpatient clinics (including the university affiliate, OHSU) refer participants for further eligibility assessment. Second, ongoing studies within our research program at OHSU and the VAPORHCS (i.e., the Sleep & Health Applied Research Program [SHARP]) referred participants to the LION study who either did not qualify for other studies or completed those other studies. Third, MTBI^2^ provides a referral service for those interested in TBI research opportunities, called the TBI Research Opportunities and Outreach for Participation in Studies (TROOPS) program. In the case of TROOPS referrals, participant confidentiality in the communication between LION and TROOPS personnel is protected using a VA-authorized end-to-end encrypted email service for all messages containing PHI/PII.

#### Website advertisement

The study utilized multiple venues for website advertisements. This included advertisements within the overall VAPORHCS website, as well as affiliated centers and labs (e.g., the VA National Center for Rehabilitative Auditory Research: www.ncrar.research.va.gov/Join_Research_Study/Index.asp). Similarly, the project is advertised on the OHSU research opportunity website, which is also shared with the OHSU Brain Institute (www.ohsu.edu/brain-institute/research-ohsu-brain-institute). Lastly, the study is listed on our research program’s website (www.sharplabpdx.com).

#### Flyers, social media, and radio

Flyers were placed in high traffic areas of the main VAPORHCS hospital and at two outpatient clinics and shared with local clinicians, study sponsors and other partners for broad dissemination. A social media post for LION was placed on the MTBI^2^ blog that also contributed participants to the overall TROOPS referral program. Other approved social media venues included Craigslist advertisements, GovDelivery (a marketing subscription email service), and other VA-approved accounts. IRB-approved visual banners and audio ads that aired on local AM radio stations were also utilized to recruit participants within the Portland-metro area. See Table 1 for the number of participants recruited via each approach.

**Table 1 pone.0305305.t001:** Interim demographic information for participants who have completed this protocol.

	MBLT (*n* = 69)		Sham (*n* = 35)	
	mTBI (*n* = 47)	No TBI (*n* = 22)	mTBI (*n* = 24)	No TBI (*n* = 11)
**Age,** *years*	53.2 ± 13.1	53.2 ± 14.8	50.9 ± 14.6	57.9 ± 15.9
**Education,** *years*	16.4 ± 1.9	15.8 ± 2.1	15.2 ± 1.9	16.2 ± 1.9
**Veteran Status**				
Veteran	46 (98%)	14 (64%)	18 (75%)	10 (91%)
Non-Veteran	1 (2%)	8 (36%)	6 (25%)	1 (9%)
**Gender**				
Man	31 (66%)	11 (50%)	17 (71%)	4 (36%)
Woman	15 (32%)	11 (50%)	7 (29%)	7 (64%)
Non-binary/other	1 (2%)	0 (0%)	0 (0%)	0 (0%)
**Race and Ethnicity**				
Ethnicity, *Hispanic/Latine*	3 (6%)	0 (0%)	2 (8%)	1 (9%)
Race, *White*	37 (79%)	14 (64%)	17 (71%)	11 (100%)
Race, *Asian*	0 (0%)	2 (9%)	1 (4%)	0 (0%)
Race, *Black of African American*	1 (2%)	4 (18%)	0 (0%)	0 (0%)
Race, *American Indian or Alaskan Native*	5 (11%)	0 (0%)	4 (17%)	0 (0%)
Race, *Two or More Races*	2 (4%)	1 (5%)	1 (4%)	0 (0%)
Race, *Other*	1 (2%)	1 (5%)	1 (4%)	0 (0%)
**Modality**				
Remote (DocuSign consent)	39 (83%)	17 (77%)	20 (83%)	5 (45%)
In-Person (Physical copy consent)	8 (17%)	5 (23%)	4 (17%)	6 (55%)
**Participant Residence Time Zone**				
Pacific Standard Time	30 (64%)	17 (77%)	20 (83%)	10 (91%)
Local Portland-Vancouver metro area	15 (32%)	8 (36%)	9 (38%)	5 (45%)
Mountain Standard Time	3 (6%)	0 (0%)	0 (0%)	0 (0%)
Central Standard Time	4 (9%)	1 (5%)	2 (8%)	0 (0%)
Eastern Standard Time	8 (17%)	4 (18%)	1 (4%)	1 (9%)
**Recruitment Method**				
Repository	3 (6%)	1 (5%)	5 (21%)	3 (27%)
Referral	11 (23%)	5 (23%)	1 (4%)	2 (18%)
Website	5 (11%)	5 (23%)	2 (8%)	0 (0%)
Flyers, social media, and radio	27 (57%)	10 (45%)	16 (67%)	4 (36%)

Data are presented as mean ± standard deviation, or *n* (%).

### Eligibility criteria

Eligibility criteria for enrollment included, over 18 years of age, able to provide informed consent and comply with the study protocol, no history of macular degeneration (contraindicated due to light therapy potentially exacerbating underlying pathology), no history of bipolar disorder (contraindicated due to light therapy potentially inciting a manic/depressive episode [31]), no shift work on third shift (e.g., 2300–0700 or equivalent) or any amount of days overnight, no current engagement in light therapy, and stable status on other pharmacological and/or behavioral sleep interventions.

This study originated in an in-person format with an exclusive focus on Veterans with mTBI, however protocol #4268 was amended to be conducted remotely, and expand recruitment to non-Veterans and to non-TBI participants, for the express purpose of increasing the diversity of this sample in terms of the number of women and individuals from racial/ethnic minority groups and increasing overall generalizability. See Table 1 for demographic parameters describing this current interim analysis.

History of mTBI was confirmed through a structured clinical interview using the Head Trauma Events Characteristics (HTEC; Table 2). The HTEC consists of a standard screening question followed by branching logic questions addressing injury type, location, intracranial injury/skull fracture, duration of loss of consciousness (LOC), and anterograde or retrograde post-traumatic amnesia (PTA), conferring a diagnosis of no, mild, moderate or severe TBI. Participants with an affirmative TBI outcome on the HTEC were excluded if their injury was moderate to severe and thus, the study only included participants with a history of mTBI. However, participants screening negative for TBI on the HTEC who met all other eligibility criteria, were also offered enrollment to promote generalizability throughout the wider VA.

**Table 2 pone.0305305.t002:** Current HTEC derived mTBI metrics.

	MBLT (*n* = 69)	Sham (*n* = 35)
	mTBI (n = 47)	mTBI (n = 24)
**Age at injury,** *years*	28.2 ± 17.4	29.6 ± 16.0
**mTBI recency,** *years*	26.2 ± 20.8	20.3 ± 15.0
**mTBI recency range**, *years*	2–67	1–52
**Number of TBIs**		
1	12 (26%)	6 (24%)
2–3	17 (36%)	6 (24%)
4–5	5 (11%)	7 (28%)
>5	11 (23%)	5 (20%)
Maximum	75	36
Average, number	6.1 ± 12.0	5.2 ± 7.4
**Type**		
Blast	1 (2%)	2 (8%)
Blunt force	5 (11%)	3 (12%)
Fall	12 (26%)	7 (28%)
Sport	4 (9%)	5 (20%)
Motor Vehicle Collision	11 (23%)	4 (16%)
Assault	2 (4%)	1 (4%)
Unknown	2 (4%)	0 (0%)
Other	10 (21%)	2 (8%)
**Loss of Consciousness**		
<5 minutes	9 (19%)	6 (25%)
5–30 minutes	13 (28%)	4 (16%)
**Post-traumatic Amnesia**, *yes*	12 (26%)	3 (13%)

Data are presented as mean ± standard deviation, or *n* (%). mTBI, mild traumatic brain injury. Type of injury and loss of consciousness data reflect participants self-reported most severe injury.

### Screening and informed consent

Eligibility screening occurred either in-person or over the phone following an IRB-approved script. Depending on the route of recruitment, some participants completed a “pre-screening” online survey via the Research Electronic Data Capture (REDCap) system. Any participants who completed this pre-screening survey received a separate phone call to complete screening prior to advancing to informed consent.

Informed consent was completed over the phone or via video conference with the participant and a study coordinator according to standard practice, which included an addendum for permission to store their data and biological samples for future analyses and studies. Consent was obtained either via physical mail of consent forms to participants’ residences together with a live phone call, or, alternatively, electronically via VA-approved DocuSign (www.docusign.com). DocuSign is an e-signature service that hosts this study’s informed consent document and HIPAA authorization for digital signatures–enabling same-day screening and consenting–and was new to the VA system as of March 2021. Digital delivery of documentation was sent using DocuSign’s encryption service with a fully signed copy sent to both the study participant and research team. Local storage of this documentation was housed on the secure, firewall-protected, VA Research Drive. Significant advantages existed using DocuSign versus physically mailing documentation back and forth, including a substantial time savings and minimization of errors (e.g., missing a signature). One caveat was that DocuSign did not adjust times when signing parties were in different time zones; therefore, in these cases, an additional Note to File was included to explain any large discrepancies in timestamps between consenters and participants.

### Randomization, allocation, and masking

After receiving informed consent, HIPAA authorization, and completing the 2-week baseline period, participants were randomized in a 2:1 allocation ratio, active intervention to sham and recorded according to the Consolidated Standards of Reporting Trials (CONSORT; Fig 3). Although participant-masked (i.e., investigators know all negative ion generators are inactive), study arms were verbally described to participants in a “pseudo” double-masked fashion, as before [28]. Specifically, all participants were informed that 50% of both study arm devices were inactive and neither they, nor us, knew whether they receive an active device until completion. After the study had been completed, a team member then disclosed to all participants their randomization status, and provided the scientific rationale necessitating the use of deception. Additionally, study investigators described these study arms as “devices”, rather than “therapies”, throughout the protocol, which was technically accurate and precluded unmasking.

**Fig 3 pone.0305305.g003:**
[figure not shown]
CONSORT diagram. The Consolidated Standards of Reporting Trails (CONSORT) diagram for participants in LION to date.

Justification for the unequal allocation ratio stems from the ethical recognition that the sham control confers no physiological benefit, whereas the active condition does [51]. However, using prior work as precedent, we anticipate greater variability in the MBLT group within key outcome metrics and thus, a 2:1 allocation ratio actually increases (albeit nominally) statistical power. Thus, this 2:1 allocation ratio is superior from an ethical perspective and better characterizes treatment dimensions in the MBLT group, ensuring the judicious use of federal funding.

